# Study protocol for a pre-registered randomised open-label trial of ten-session cognitive behaviour therapy (CBT-T) for eating disorders: does stratified augmented treatment lead to better outcomes?

**DOI:** 10.1136/bmjopen-2025-099212

**Published:** 2025-04-25

**Keywords:** Eating disorders, Clinical Trial, MENTAL HEALTH

## Abstract

**Introduction:**

Further improvement of cognitive–behavioural therapy for eating disorders (CBT-ED) is required that can provide better outcomes. Recent work showed that the length of therapy is not critical in improving outcomes. Rather, stratifying the treatment to individual needs is required to produce significant improvements. The current study adopts the approach of evaluating augmentations to ten-session CBT (CBT-T) where initial response to therapy is gradual rather than rapid.

**Methods and analysis:**

Clients aged 15 years and over presenting to the Flinders University Services for Eating Disorders between January 2025 and June 2028 will be randomised to receive either CBT-T as usual or CBT-T augmented with therapy modules (CBT-TA) matched to obstacles to progress for gradual responders. Rapid response, assessed using the Eating Disorder Examination Questionnaire, is defined as ≥1.13 decrease in global ED psychopathology at session 4. In CBT-TA, the therapist and gradual responder will collaboratively choose at least one of nine augmentations to incorporate into therapy. Rapid responders in this group will be given access to the augmentations for use in their own time. Data for the main intent-to-treat analyses will be collected on five occasions: baseline assessment (T1), immediately preceding session 4 (T2), end of treatment (T3) and 3-month and 6-month follow-up (T4 and T5). The primary outcome is ED psychopathology, and secondary outcomes include behavioural indicators of the ED, impairment caused by the ED, general negative emotion, self-harm and hope. Analyses will be undertaken on an intention-to-treat basis and will include all participants in the group to which they were randomised.

**Ethics and dissemination:**

Ethics approval was provided by the Social and Behavioural Research Ethics Committee at Flinders University (7992). This trial was prospectively registered with the Australian New Zealand Clinical Trials Registry (ACTRN12624001495516). The findings arising from the study protocol will be reported to participants and presented at scientific conferences and disseminated by publications submitted to peer-reviewed journals.

**Trial registration number:**

Australian New Zealand Clinical Trials Registry (ACTRN12624001495516).

STRENGTHS AND LIMITATIONS OF THIS STUDYThis parallel two-arm randomised controlled trial examines the benefit of adding augmentation to treatment as usual for non-underweight people with eating disorders.This is not an adaptive trial design but will evaluate an adaptive treatment strategy for 10-session cognitive–behavioural therapy (CBT) for eating disorders.We will randomise 162 participants to augmented CBT and 68 participants to the non-augmented CBT ensuring sufficient power.Gradual responders in the augmented CBT arm will get access to one of nine treatment augmentations designed to tackle obstacles to progress.A limitation of the research is that repeated measures assessment of eating disorder psychopathology relies on self-report questionnaires.

## Introduction

 While large within-group effect sizes are obtained for eating disorder (ED) treatments using cognitive–behavioural therapy (CBT) in routine clinical care, with a mean attrition rate of 25.5%,^1^ CBT for bulimia nervosa produces abstinence in only 37.5% of completers.^2^ Further improvement of CBT for EDs (CBT-ED) is required that can provide better outcomes. Recent work shows that the length of therapy is not critical in improving outcomes. A meta-analysis of ten-session CBT (CBT-T) for non-underweight people (ie, excluding anorexia nervosa)^3^ showed pooled within-group effect size (Cohen’s d) reduction in ED psychopathology of −1.49 (−1.68 to −1.31). This is a similar effect size reduction in ED psychopathology achieved by 20-session enhanced CBT, ranging from −1.32 (–1.67 to −0.97)^4^ to 1.79 (−2.21 to −1.37).^5^ CBT-T has five phases, including early dietary change and exposure, behavioural experiments related to food, addressing emotional triggers, body image work and relapse prevention. A key difference from longer forms of CBT-ED is that behavioural and dietary change are stressed from the very outset of treatment rather than being delayed.

Meta-analytic evidence addressing the outcomes of mental health interventions suggests several pathways to producing improvements. First, early change is one of the strongest and most replicable predictors of therapy outcome,^6 7^ with studies of eating disorder treatment measuring this between sessions 3 and 9.^8^ It is also the time when most of the overall change of therapy occurs.^9^,^12^ In CBT-T, two distinctive groups of people receiving therapy can be identified: those who experience ‘rapid response’ and those who experience ‘gradual response’. The former group can be identified as achieving a ≥1.13 decrease in ED psychopathology as measured with the Eating Disorder Examination Questionnaire (EDE-Q),^13^ quantified by Bell and colleagues^14^ using the reliable change index across 164 adults receiving outpatient treatments for EDs. While Bell *et al* considered this change by session 8, subsequent research has shown that it is an effective level of change for identifying early responders at session 4. Application of this decrease by session 4 in a sample of 176 people receiving CBT-T, rapid responders (58% of those commencing treatment) were 2.5 times more likely to meet remission criteria at end of treatment than gradual responders.^15^ At the end of treatment, rapid responders had a significantly lower level of ED psychopathology than gradual responders, with a between-group effect size (Cohen’s d) of −1.11 (−1.50 to −0.72).^15^

Second, stratifying treatment such that it is matched to the individual profile (ie, personalised treatment) improves treatment outcomes. A small but significant effect size favours personalised treatment relative to standardised treatment.^16^ In EDs, the use of stratified treatment for gradual responders has been shown to produce commensurate outcomes between rapid and gradual responders.^17^ Additionally, building in some degree of individual choice and tailoring as to therapy components produces a significant benefit over purely clinician-tailored options.^18^

Third, acute augmentation (defined as interventions delivered immediately before, during or after a session of manualised psychological therapy with the aim of enhancing the impact of the therapy, either as a single intervention or across multiple therapy sessions) of ED treatment has also been shown to significantly improve outcomes over therapy alone with no augmentation.^19^ These acute augmentations are designed to be delivered on at least one occasion and can be repeated but are not offered concurrently over the whole of the treatment duration.

Currently, only five trials in ED exist that use stratified treatment for gradual responders.^15^ To date, none have built in participant choice for personalisation of treatment. This collaborative decision-making is recommended in clinical practice for EDs,^20^ but no rigorous evaluation exists of this practice. We describe a CBT-T treatment protocol designed to reduce the outcome gap between rapid and gradual responders compared with our previous three evaluations of CBT-T.^15^ This augmented treatment, CBT-TA, differs from CBT-T in four main ways: (1) while the first three sessions of the two treatments do not differ, we will now use an a priori indicator based on the global EDE-Q score to differentiate rapid (EDE-Q ≥1.13) and gradual (EDE-Q <1.13) responders before the start of session 4; (2) in the CBT-TA group, gradual responders will have a collaborative discussion with the therapist as to the barriers to more rapid change; (3) these barriers will be matched to nine possible treatment augmentations, identified by a Delphi consensus study across four different panels: people with lived experience, significant others, clinicians and researchers; requiring 80% of participants from all four panels to rate a statement as either ‘Essential’ or ‘Important’ for the statement to be endorsed;^21^ and (4) the gradual responders will receive their choice from nine augmentations, which will be tackled within sessions in addition to treatment as usual over the next five sessions of therapy. In the CBT-TA group, rapid responders will be given access to the platform housing the augmentations, but this content will not be discussed in therapy.

This protocol is reported following Standard Protocol Items: Recommendations for Interventional Trials guidelines.^22^ The overall aim of this randomised controlled trial is to evaluate the comparative effectiveness and acceptability of CBT-T for non-underweight clients with EDs aged 15 years and above to CBT-TA. To achieve this, participants will be randomised to either receive CBT-T or CBT-TA. Our first specific aim is to examine superiority of CBT-TA (in clinically determined gradual responders) against a CBT-T control group. The secondary research aim is to examine superiority of CBT-TA (in clinically determined rapid responders) against a CBT-T control group. We also will address an exploratory aim, namely, whether any differences exist between CBT-TA (passive augmentation) in clinically determined rapid responders vs CBT-TA (active augmentation) clinically determined gradual responders.

First, we hypothesise that gradual responders in CBT-TA will have significantly lower ED psychopathology compared with gradual responders in CBT-T at end of treatment and that these gains will be maintained at the 3-month and 6-month follow-up. We also hypothesise that remission will be higher in the former than latter group. Second, we hypothesise the same advantages for the rapid responder group in CBT-TA over rapid responders in CBT-T. We will also explore (1) change in health service utilisation including primary, secondary and tertiary care, (2) engagement and completion data between the two conditions to establish the relative acceptability of the interventions, and (3) client’s experiences of therapy in the form of qualitative feedback.

## Methods and analysis

### Study design

The study is a parallel two-arm randomised controlled trial (see figure 1). Demographic data will be collected via the online referral then the full online assessment schedule will occur at baseline assessment (T1) which precedes face-to-face assessment with a therapist to finalise eligibility and desire to engage in CBT-T. Further evaluation of engagement and commitment to therapy will be conducted by asking clients to complete a behavioural activation single session intervention (BA-SSI) over the next 2-week period, at the end of which time (i) ED psychopathology will be assessed online again; (ii) level of engagement with the BA-SSI will be assessed; and (iii) randomisation will occur with the first therapy session occurring within a week. T2 will be conducted immediately preceding session 4, to inform extent of response. Assessments will be repeated at the end of treatment (T3) and 3-month and 6-month follow-up (T4 and T5). T3 will occur 10 weeks post-randomisation (12 weeks post-baseline). T4 and T5 will occur 22 and 34 weeks post-randomisation (24 and 36 weeks post-baseline respectively).

**Figure 1 F1:**
[figure not shown]
Study design.

### Study setting

The study will be conducted at the outpatient Flinders University Services for Eating Disorders (FUSED) in South Australia. Previous descriptions of four clinical trials from FUSED have been published,^23^,^26^ each including participants aged 15 years and above. The completer remission rate for CBT-T in our clinic is 36%,^15^ consistent with meta-analytic data for CBT for ED.^2^ In the current study, the CBT-T therapy will be conducted face-to-face by a mix of clinical psychology postgraduate trainees and registered clinical psychologists, under expert supervision. All data are self-reported and will be collected online via the Qualtrics survey platform. Participants can be self-referred or referred by a primary or mental health professional.

### Eligibility criteria

Eligible participants (1) are aged 15 years and over; (2) have any DSM-5 diagnosis of ED as determined by the EDA-5 online clinical interview (https://eda5.org/) excluding anorexia nervosa and avoidant/restrictive feeding intake disorder for which no evidence of the efficacy of CBT-T exists; (3) consent to FUSED communicating regularly with their general practitioner; (4) reside in South Australia; and (5) can read independently at grade 2 level English. The age inclusion was informed by research^27^ showing that adolescents with an eating disorder and a mean age of 15 years self-select CBT rather than family-based treatment. Participants are not eligible if they report current life-threatening suicidal ideation, untreated psychosis, or substance dependence, or have a Body Mass Index (BMI)<18.5 (or BMI-for-age <5th percentile if an adolescent), or currently receiving a psychological therapy for an ED. Eligibility criteria will be assessed at the screening assessment and checked again in the face-to-face assessment.

### Patient and public involvement

The CBT-T protocol^28^ for this study was developed with extensive engagement of clinicians experienced in the delivery of CBT-ED and is associated with a meta-analysis summarising effects across 10 different evaluations.^3^ The focus of the nine therapy augmentations was decided by a Delphi consensus method, conducted online across four different panels: people with lived experience, significant others, clinicians and researchers.^21^ The nine targets or processes include: (1) basing self-worth on one or two aspects of oneself; (2) persistent and excessively high standards; (3) poor distress tolerance skills and emotion regulation problems; (4) being self-critical; (5) negative body image; (6) low self-compassion; (7) low self-worth and self-acceptance; (8) social isolation; and (9) unhelpful thinking habits. The augmentations will be interventions that have robust evidence for ability to improve these processes (eg, behavioural activation for emotional regulation or social isolation) delivered via online interactive documents that have been co-designed with our expert advisory panel, consisting of people with lived experience, carers, researchers and clinicians.

### Interventions

The CBT-T protocol^28^ forms the basis of both intervention arms. The assessment period for both the CBT-T and CBT-TA arms is designed to encourage change and treatment retention and improve treatment outcome before treatment commences. First, the face-to-face assessment will include motivational enhancement exercises that have been shown to significantly improve outcomes for less motivated clients.^25^ Second, completion of an SSI between the assessment and start of therapy has been shown to significantly increase completion of the 10 therapy sessions.^26^ Third, our current, unpublished research shows that use of the BA-SSI (as an interactive document available at https://osf.io/xpqa8/) in the 2-week period between assessment and treatment significantly reduces ED psychopathology in 69% of participants. This suggests that early change sets them up for better outcomes in treatment.

The intervention comprises of 10 face-to-face sessions with each session lasting approximately 50 min. The CBT-T protocol which describes the structure of each session in detail is available on the CBT-T website: https://cbt-t.sites.sheffield.ac.uk/resources. A further three sessions will be scheduled after treatment ceases to ensure that progress is maintained (1, 3 and 6 months post-treatment); assessment will only be conducted at 3-month and 6-month follow-up (T4, T5).

In CBT-T, a review of engagement and progress is routinely conducted in session 4, where those who are not engaging in therapy (eg, are not actively doing the therapy homework tasks every day between sessions, such as food monitoring, exposure tasks) are invited to step away from treatment until circumstances allow them to fully commit to doing therapy, or to have one final attempt to engage by session 5. In the current study, progress will be examined using sessional assessment with the ED15.^29^ Rapid response will be classified as a ≥1.13 decrease in global ED psychopathology by session 4 as measured with the EDE-Q.^13^

Novel to this study, CBT-TA will give participants access to nine treatment augmentations in the form of an interactive document. The gradual responders will be engaged in discussion at session 4 to examine barriers to rapid change and which of the augmentations may best address these. The augmentations will then be incorporated into ongoing therapy. The rapid responders will be made aware of the treatment augmentations and how to locate them, but they will not be incorporated into ongoing therapy.

### Procedure and participant Timeline

Figure 1 outlines the study flow and table 1 outlines the schedule of enrolments, interventions and assessments. People can self-refer by contacting the FUSED email ([contact]) or be referred by a primary health (eg, general practitioner) or mental health professional. [name]’s Flinders University website contains a link (https://www.flinders.edu.au/engage/community/clinics/flinders-university-services-eating-disorders) to information about the study. People wishing to proceed to a face-to-face assessment will either, depending on therapist availability, (**i**) be placed on a waitlist or (ii) be emailed with a date for an assessment appointment and a Qualtrics link to the T1 assessment and online consent, to be completed before the appointment. People under the age of 18 years require parental consent as well as their personal assent. The study and the requirements of therapy will be explained in the face-to-face assessment, and participants who are interested in doing therapy will be asked to sign consent to allow FUSED to contact their general practitioner and other professionals involved in their care.

**Table 1 T1:** Schedule of assessment

Timepoint	Initial assessment	Pre-treatment				
	T_1_		T_2–S4_	T_3–S10_	T_4–FU1_	T_5–FU2_
Enrolment:
Eligibility screen	X
Informed consent	X
Given BA-SSI to complete	X
Allocation	X
Interventions:
CBT-T				
CBT-TA				
Assessments:
Eating Disorder Examination-Questionnaire	X	X	X	X	X	X
Service use	X	X
General negative emotion (DASS)	X	X	X	X	X
Inventory of Statements About Self-Injury (ISAS) Section I: Behaviours	X	X	X	X	X
(ISAS) Section II: Functions	X
Clinical Impairment Questionnaire	X	X	X	X	X
Adult State Hope Scale	X	X	X	X	X
BA-SSI completion	X
Qualitative feedback: worst and best things about therapy	X
ED15 (used before each session)	X	X	X	X	X

BA-SSI, behavioural activation single session intervention; CBT-T, ten-session cognitive–behavioural therapy.

Following the baseline assessment, participants are given the BA-SSI (either in hard copy or emailed as an interactive document) and an appointment for a first session of therapy will be made for 2 weeks post-assessment. A follow-up email will be sent to the participant containing the Qualtrics link for the T2 assessment, to be completed before the first session of therapy. If this is not completed by the morning of the scheduled appointment, the therapy will not proceed, and the participant will be contacted as to whether they wish to pursue therapy. If they do not proceed into the study, a letter will be sent to them and shared with their general practitioner, summarising the assessment and treatment needs, and alternative services.

Once the participant attends the first therapy appointment, randomisation of the participant to either the CBT-T or CBT-TA condition will be recorded. The therapist and client will be blind to this allocation and will be informed of randomisation between sessions 3 and 4 of therapy.

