Analyses will be undertaken with a treatment-policy approach (ie, intention-to-treat) and will include all participants in the group to which they were randomised, regardless of actual receipt or uptake of the intervention or withdrawal from the study (ICH E9 R1^45^). Mixed-model repeated measures analysis will be used for the continuously scaled primary outcome and secondary outcome variables. An unstructured residual variance-covariance matrix will accommodate within-participant dependency. The model will include factors of study condition (CBT-T, CBT-TA), occasion of measurement (baseline, 4, 10, 22 and 34 weeks post-randomisation) and their interaction as fixed effects, with a random intercept to account for variation between individual participants. The primary outcome will be assessed by a planned comparison of the difference between groups in change of the primary outcome variables over time. Given the assumption of MRMM that data are missing at random (MAR), multiple imputation will be used to replace missing observations. To examine robustness of the results and the MAR assumption, sensitivity analyses will be conducted using the tipping point and delta adjustment method. Additionally, we will run a number needed to treat analysis, based on the proportion of participants in each arm who meet the prespecified criteria for remission,^46^ (i) global EDE-Q score ≤2.77, (ii) BMI ≥18.5 and (iii) no ED behaviours in the previous 1 month period.

Analyses of secondary outcome variables will follow the same methods as the primary outcome except for the behavioural count variables, which will be analysed with generalised linear mixed modelling (GLMM). Separate GLMM models with a log link function and gamma distribution will be used to account for the right skewed health utilisation data.

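### The EDE-Q taken before session 1 is mislabelled T2 and left out of the primary model, which costs precision but does not bias the comparison of arms

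*Protocol article*

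**What the plan says.** The protocol article uses the label T2 for two different assessments.

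- Abstract: the five occasions are "baseline assessment (T1), immediately preceding session 4 (T2), end of treatment (T3) and 3-month and 6-month follow-up (T4 and T5").
- Study design: "T2 will be conducted immediately preceding session 4, to inform extent of response". Table 1 agrees and heads that column as the session 4 assessment.
- Procedure and participant timeline: the follow-up email carries the "Qualtrics link for the T2 assessment, to be completed before the first session of therapy".

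The assessment before session 1 does exist. Study design says that at the end of the two-week BA-SSI period "ED psychopathology will be assessed online again", without giving that occasion a T-number. Table 1 has an unnumbered pre-treatment column and six EDE-Q marks. The assessment is compulsory: "If this is not completed by the morning of the scheduled appointment, the therapy will not proceed".

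The Data collection, management and statistical analysis section lists five occasions for the model, "occasion of measurement (baseline, 4, 10, 22 and 34 weeks post-randomisation"). Condition, occasion and their interaction are the fixed effects, and the planned comparison is the difference between groups in change over time. Between T1 and session 1 every participant is given the BA-SSI, which the Interventions section says "significantly reduces ED psychopathology in 69% of participants".

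**The concern.** There are two linked problems. First, one label stands for two time points of the primary outcome measure, so the text cannot be right in both places.

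Second, of the six EDE-Q scores collected, the model leaves out the one closest to allocation. It works from T1, which lies further back and on the other side of an intervention that, by the article's own account, moves scores. The omitted score costs nothing more to obtain. If it predicts outcome beyond T1, leaving it out gives away precision. This trial has little to spare: it plans for 40% attrition, and its first aim concerns only the gradual responders, taken as 42% of participants.

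**Working it through.** **1. Which score is omitted.** EDE-Q occasions collected (Table 1): T1, pre-treatment, session 4, session 10, first follow-up and second follow-up, six in all. Occasions modelled: baseline and weeks 4, 10, 22 and 34, five in all. The abstract equates baseline with T1. Study design puts T3 at 10 weeks post-randomisation and 12 weeks post-baseline, so baseline lies 12 − 10 = 2 weeks before randomisation, which is the length of the BA-SSI period. The missing occasion is therefore the one before session 1.

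**2. Whether it is a legitimate baseline covariate.** Study design lists the repeat EDE-Q ahead of randomisation. The Procedure section records randomisation once session 1 is attended, and the Randomisation and blinding section places it after session 1. The score precedes allocation on each account. In addition, sessions 1 to 3 are the same in both arms and allocation is not disclosed until between sessions 3 and 4, so treatment cannot have affected it. In the Procedure section's sequence, nobody reaches session 1, and so randomisation, without it.

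**3. The plan's own figure.** The stated sample size reproduces, so it is not what is wrong here. Inputs (Sample size and Randomisation sections): d = 0.35, power 0.80, alpha 0.05 (taken as two-sided), r = 0.50, ratio 2.4:1, five waves, 10% attrition per wave (retention 0.9^k for k = 0 to 4). For a group difference averaged over the waves with equal correlations, the relative variance is 0.7455 and

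n(CBT-T) = (1 + 1/2.4) × (1.960 + 0.842)² × 0.7455 / 0.35² = 67.7.

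Then n(CBT-TA) = 2.4 × 67.7 ≈ 162.4, and the total is about 230.

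**4. Relative variance of the treatment contrast at one follow-up occasion.** This takes complete data and equal variances, with the variance of a simple post-treatment comparison set to 1.

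- Baseline as a level of occasion, contrast in change: 2(1 − r) = 2(1 − 0.50) = 1.00.
- T1 as covariate: 1 − r² = 1 − 0.25 = 0.75.
- T1 and the pre-session-1 score as covariates: 1 − R², where R² = (g₁² + g₂² − 2ρg₁g₂)/(1 − ρ²). Here g₁ = 0.50 is the correlation of T1 with outcome (stated), g₂ that of the pre-session-1 score with outcome (assumed), and ρ the correlation between the two scores (assumed).

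| g₂ | ρ | R² | 1 − R² | relative to 0.75 |
|---|---|---|---|---|
| 0.5 | 0.9 | 0.05/0.19 = 0.263 | 0.737 | 0.98 |
| 0.5 | 0.7 | 0.15/0.51 = 0.294 | 0.706 | 0.94 |
| 0.6 | 0.9 | 0.07/0.19 = 0.368 | 0.632 | 0.84 |
| 0.6 | 0.7 | 0.19/0.51 = 0.373 | 0.627 | 0.84 |

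**5. Where the added gain vanishes.** The second score adds nothing when g₂ = ρg₁, for example at g₂ = 0.9 × 0.5 = 0.45 with ρ = 0.9, or g₂ = 0.7 × 0.5 = 0.35 with ρ = 0.7. The 2% in the first row is therefore not a floor.

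**The case against.** **Bias.** A reader might infer that a baseline taken before the BA-SSI distorts the treatment effect. The documents do not support that. Both arms receive the BA-SSI before allocation, so its effect is common to both and cancels in the randomised contrast. It enters only the description of change within each arm. Treating the BA-SSI as part of the assessment period and measuring from T1 is a defensible design choice.

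**Mix-up.** A reader might also infer that the pre-session-1 score could be entered as the week-4 value. That is unlikely: the analysis section names occasions by week, and Table 1 shows the two columns separately. The Procedure section reads as one stray label.

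**Not a clean post-BA-SSI baseline.** The EDE-Q asks about the past 28 days and this score comes about two weeks after T1, so roughly half its recall window lies before T1. This stands. The score is useful as a predictor, but it does not separate BA-SSI change from therapy change.

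**Size.** Only the 0.50 is in the documents. The gain from the second score rests on assumed correlations. Set against 230 participants, the 2% to 16% reduction from 0.75 is worth about 4 to 45 people (230 × (0.75/0.737 − 1) to 230 × (0.75/0.627 − 1)). On the roughly 97 gradual responders (0.42 × 230) it is worth about 2 to 19. This stands as well.

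**Left to the SAP.** The choice of covariates often is, and no SAP is shown. But the article does not stay silent: it fixes the occasions and makes baseline a level of the occasion factor. That stated choice is what is questioned.

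**Conclusion.** The labelling contradiction is certain and needs correcting. The modelling point holds as one of efficiency, not validity: the model passes over a valid pre-randomisation score that is complete by design, and saves nothing by doing so.

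The larger and better supported part of the gain comes from moving T1 out of the response and into the covariates: relative variance falls from 1.00 to 0.75 at the article's own r = 0.50. Adding the pre-session-1 score brings it to about 0.63 to 0.74 under the assumed correlations, and possibly no lower than about 0.75 if that score predicts outcome less well than T1. These figures refer to a single follow-up occasion with complete data and equal variances; missing data and averaging over occasions would change them.

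**What to change.** 1. Give the pre-session-1 EDE-Q its own label in the Procedure section, the Study design section and Table 1, and keep T2 for the assessment before session 4.
2. In the analysis section, take the post-randomisation occasions (weeks 4, 10, 22 and 34) as the response. Remove T1 from the response and enter T1 and the pre-session-1 EDE-Q as baseline covariates, each interacting with occasion. Include both in the imputation model too, so that it matches the analysis.
3. There is no need to redefine change from the pre-session-1 score: once it is a covariate, doing so leaves the treatment contrast unchanged.

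The cost is a wording change and one or two extra covariates with their occasion interactions. No further data collection is needed.
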